#### 1.2.2. Theoretical Frameworks: EPF, WCC and NCH

Three influential cognitive models, namely, Enhanced Perceptual Functioning (EPF), Weak Central Coherence (WCC), and the Neural Complexity Hypothesis (NCH), offer complementary explanations for these integration difficulties. These frameworks are particularly relevant when considering levels of complexity involving phonological features such as consonants (C) and vowels (V) as local, segmental units, and tone (T), as well as combinations like C + V, V + T, C + T, and C + V + T, as global, integrative features.

WCC posits a cognitive style in ASD that favors local detail processing at the expense of global integration [50]. Applied to speech, this suggests that children with ASD may process individual acoustic cues (e.g., formants) accurately but struggle to bind them into unified linguistic percepts. In contrast, EPF reframes this dissociation: rather than a deficit in global processing, it attributes the pattern to heightened sensitivity to local sensory inputs [51]. This can lead to “perceptual encapsulation,” where low-level features are processed in isolation, interfering with holistic integration. In line with WCC and EPF, individuals with ASD may demonstrate intact or heightened sensitivity to isolated, segmental features such as consonants or vowels while showing weakened neural responses to complex, multi-feature contrasts, including lexical tone or dual/triple feature combinations.

NCH further proposes that individuals with ASD may show intact or enhanced processing of simple stimuli, but progressively impaired responses as stimulus complexity increases [52]. Consistent with the NCH, meta-analytic findings show enhanced pitch discrimination in ASD, but also differences in how pitch is integrated into broader linguistic or musical contexts, suggesting a dissociation between basic auditory encoding and more complex integration processes [18].

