### 1.4. The Current Study

A key innovation of this study is the fine-grained analysis of auditory mismatch responses across varying levels of speech feature complexity. Unlike previous research, which has largely focused on isolated speech elements such as pitch, vowels, or consonants, and thus neglected their dynamic interplay, we aim to investigate how segmental (e.g., consonants, vowels) and suprasegmental (e.g., tone) features are processed and integrated in Mandarin-speaking children with ASD.

We employ a multi-feature oddball paradigm to examine whether children with ASD differ from typically developing (TD) peers in their sensitivity to single-, dual-, and triple-feature speech deviations. Neural responses will be assessed via the mismatch negativity (MMN), focusing on differences in amplitude, latency, and temporal coordination across processing stages. Although the P3a component is sometimes analyzed in the literature, its inconsistent reporting means it will not be a primary focus of our exploratory study.

Our study addresses four key questions:Do children with ASD show diminished MMN responses to speech feature deviations, with greater impairment for complex, multi-feature contrasts?Do ERP differences reflect processing delays that cascade across time, rather than isolated amplitude reductions?How do concurrent changes in tone, consonant, and vowel interact in ERP responses, and do children with ASD show atypical integration patterns in MMN?Given tone’s lexical role in Mandarin, do children with ASD show the most pronounced differences in tone-related conditions, suggesting a language-specific signature of speech processing difficulty?

To address these questions, we adopt a dual-framework approach that distinguishes between theory-driven and data-driven hypotheses. Our theoretical framework integrates three complementary models, WCC, EPF, and NCH, to explain auditory processing in ASD. Together, these models suggest a dissociation as our central hypothesis with specific prediction outlined in Table 1: enhanced or intact MMN responses to single-feature deviants (e.g., consonant or vowel changes), but attenuated or delayed responses to multi-feature deviants (e.g., C + V, V + T, C + V + T), reflecting impaired integration under increasing cognitive load. In this framework, consonants and vowels are tentatively classified as local, segmental features, while tone and multi-feature combinations are treated as global, integrative features.

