#### 3.1.1. t-PCA-Level Predictions (P)

P1 (Component Variance): The proportion of variance explained by temporally decomposed MMN components (eMMN, lMMN) will be lower in the ASD group for multi-feature deviants (V + T, C + T, C + V + T), reflecting less structured neural responses under high integrative demand.

P2 (Factor Scores): Factor scores for MMN-related components will be significantly reduced in the ASD group, particularly for tone-involving conditions (T, V + T, C + T, C + V + T), consistent with a global integration deficit.

P3 (Temporal Dynamics): The ASD group will show a delayed peak in late MMN (lMMN) components across all conditions, with the greatest delay observed for triple-feature deviants, supporting NCH’s prediction of cascading processing delays.

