**Figure 3 brainsci-15-00905-f003:**
[figure not shown]
Workflow of RSA applied to ERP data from a multi-feature oddball paradigm.

**Table 1 brainsci-15-00905-t001:** Tentative Predictions for the Seven Stimulus Conditions (Based on EPF/WCC/NCH) Condition.

	Processing Type	Prediction in ASD	EPF + NCH Account	WCC + NCH Account
Consonant only	Local	↑ or = MMN amplitude ↓ or = MMN latency	Enhanced perception of phonetic detail	Intact
Vowel only	Local	↑ or = MMN amplitude ↓ or = MMN latency	Enhanced formant processing	Intact
Tone only	Global	↓ MMN amplitude ↑ MMN latency	Reduced prosodic integration	Impaired due to global integration load
C + V	Mixed/Global	↓ MMN amplitude ↑ MMN latency	Disruption due to multiple feature load	Integration weakness
V + T	Global	↓↓ MMN amplitude ↑↑ MMN latency	Disrupted holistic processing	Poor feature binding
C + T	Global	↓↓ MMN amplitude ↑↑ MMN latency	Disrupted holistic processing	Failure to form unified percept
C + V + T	Global	↓↓↓ MMN amplitude ↑↑↑ MMN latency	Collapsed integration under complexity	Strongest integration failure

Note: ↑ represents significant increase. ↓ represents significant decrease. = represents similar results when comparing MMN responses in ASD group with those in the TD group. Double/Triple arrows indicate magnitude increment/decrement.

**Table 2 brainsci-15-00905-t002:** Specific Predictions Based on MMN Literature-Based Predictions for Each Stimulus Condition.

Condition	MMN Amplitude in ASD	Latency in ASD	Reduced Left-Hemispheric MMN Dominance
Consonant only	↓	↑	Predicted—based on broader speech processing literature
Vowel only	= or ↓	↑	Predicted—but may be less pronounced than for consonants
Tone only	↓	= or ↑	Predicted—particularly for lexical tones
C + V	↓↓	↑↑	Predicted—likely pronounced
V + T	↓↓	↑↑	Predicted—key for tonal languages
C + T	↓↓	↑↑	Predicted—reflects integration challenge
C + V + T	↓↓↓	↑↑↑	Predicted—most pronounced reduction expected

Note: ↑ represents significant increase. ↓ represents significant decrease. = represents similar results when comparing MMN responses in ASD group with those in the TD group. Double/Triple arrows indicate magnitude increment/decrement.

**Table 3 brainsci-15-00905-t003:** Phonological Stimuli: Standard vs. Deviant Feature Variations.

Stimulus Type	Stimulus	Feature(s) Changed
Standard	/ba1/	None
Deviant 1	/ba4/	Tone change
Deviant 2	/bu1/	Vowel change
Deviant 3	/da1/	Consonant change
Deviant 4	/bu4/	Tone + Vowel Change

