Deviant 5	/da4/	Tone + Consonant Change
Deviant 6	/du1/	Vowel + Consonant Change
Deviant 7	/du4/	Tone + Vowel + Consonant Change

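### P1 leaves C + V, the only tone-free combination, out of its multi-feature deviants, so a deficit confined to tone satisfies it and is read as an effect of integrative demand

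*Protocol article*

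**What the plan says.** Four places in the protocol article define or use the set of multi-feature conditions.

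- **Section 1.2.2** treats "combinations like C + V, V + T, C + T, and C + V + T, as global, integrative features".
- **Section 1.4** gives the theory-driven central hypothesis as enhanced or intact responses to single features but "attenuated or delayed responses to multi-feature deviants (e.g., C + V, V + T, C + V + T), reflecting impaired integration under increasing cognitive load". The list there is introduced as examples, and C + V comes first.
- **Table 1** types C + V as Mixed/Global and predicts lower amplitude and longer latency in ASD. One account gives the reason as "Disruption due to multiple feature load", the other as a weakness of integration.
- **Section 3.1.1, P1** predicts that the proportion of variance explained "will be lower in the ASD group for multi-feature deviants (V + T, C + T, C + V + T"). This list is not marked as examples, and C + V is absent. The reading that P1 attaches to a lower value is "reflecting less structured neural responses under high integrative demand".

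P2, in the same section, predicts reduced factor scores, "particularly for tone-involving conditions (T, V + T, C + T, C + V + T), consistent with a global integration deficit".

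Table 3 shows that the C + V deviant is presented: Deviant 6, /du1/, is labelled "Vowel + Consonant Change".

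Section 1.4 also keeps two issues apart. Questions 1 and 3 ask about feature load and integration. Question 4 asks whether tone-related conditions are the most affected, as a language-specific signature.

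**The concern.** P1 uses the term multi-feature for a narrower set than the hypothesis it is meant to test, and gives no reason. The condition it drops is the informative one. In C + V, a deficit confined to tone predicts no group difference, while an integration deficit predicts one. In the other three combinations both accounts predict a difference.

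As worded, P1 can be confirmed by children who have difficulty with tone and none with combining features, and the stated reading would then be integrative demand. P2 raises a related problem of interpretation: a reduction seen only in its listed conditions would be called a global integration deficit, although a tone deficit produces the same pattern. What is at stake is whether the answers to Questions 1 and 3 can be told apart from the answer to Question 4.

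**Working it through.** The point concerns which conditions belong to a set. The plan states no figure to reproduce.

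**1. Code the seven deviants (Table 3) and compare the sets.**

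| Deviant | Tone change? | Multi-feature in 1.2.2 / Table 1 | P1 list | P2 list |
|---|---|---|---|---|
| C | no | no | no | no |
| V | no | no | no | no |
| T | yes | no | no | yes |
| C + V | **no** | **yes** | **no** | no |
| V + T | yes | yes | yes | yes |
| C + T | yes | yes | yes | yes |
| C + V + T | yes | yes | yes | yes |

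Tone is present in 3 of 4 combinations in the design, 3 of 3 in P1, and 4 of 4 conditions in P2.

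**2. Apply two simple deficit patterns.**

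- *Tone only*: every deviant containing tone is reduced, nothing else.
- *Integration only*: every deviant with two or more features is reduced, single features intact.

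| Pattern | P1 met in full | P2 list met in full | P1 with C + V added |
|---|---|---|---|
| Tone only | yes | yes | **no** |
| Integration only | yes | no (T intact) | yes |

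P1 as written cannot separate the two patterns. With C + V added, it fails under the tone-only pattern.

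**3. Find a contrast that isolates integration.** Work with deviant-minus-standard responses. Let ASD have deficits c, v and t for the single features, carried over additively into the combinations, plus an extra deficit g when consonant and vowel change together. The deficits are then c for C, v for V, and c + v + g for C + V.

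- (C+V) − C − V: (c + v + g) − c − v = **g**. It is zero under a deficit confined to tone, consonant or vowel.
- (C+V) − mean(C, V): c + v + g − (c + v)/2 = g + (c + v)/2. Under a consonant-only deficit δ this is 0.5δ, not zero. Averaging the single features is therefore not a clean test, even though tone is balanced.

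**4. Price the clean contrast.** Assume equal variances of 1 and a common correlation ρ between conditions. Neither is given in the article.

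- Variance of (C+V) − C − V: 3 + 2ρ(−1 − 1 + 1) = 3 − 2ρ.
- Variance of the mean of P1's three conditions minus the mean of C, V and T: (1 − ρ)(1/3 + 1/3).

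| ρ | SD, (C+V) − C − V | SD, pooled contrast | Ratio |
|---|---|---|---|
| 0.3 | √2.4 = 1.55 | √0.467 = 0.68 | 2.27 |
| 0.5 | √2.0 = 1.41 | √0.333 = 0.58 | 2.45 |
| 0.7 | √1.6 = 1.26 | √0.200 = 0.45 | 2.83 |

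With 30 per group, two-sided 0.05 and g = 0.5 SD (assumed), the noncentrality is (0.5/SD)·√(30/2). The two-sample t power is about 23%, 27% and 32% for ρ = 0.3, 0.5 and 0.7.

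**The case against.** **P1's selection has some basis in Table 1.** Its three conditions are the combinations typed Global with double or triple arrows; C + V is Mixed/Global with single arrows. This may explain the choice, but P1 says multi-feature, not strongly global, and does not say that it restricts the set. The mismatch stands.

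**Tone counts as global in this framework.** Sections 1.2.2 and 1.4 class tone alone with the integrative features, so a tone deficit is part of the prediction. That is fair as far as it goes. But the authors call the classification provisional, and Question 4 poses the tone-specific account separately.

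**A reader might infer that P2 is also contradictory.** It is not. P2 labels its list as tone-involving, so a tone-free condition does not belong there, and the word particularly leaves the prediction open to others. Only the interpretation attached to it needs a condition.

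**A reader might infer that an intact C + V would count against nothing in the plan.** That goes too far. Table 1 and the central hypothesis predict a C + V deficit, so an intact C + V already counts against the theory-driven account. P3 and P10 cover all conditions, and P7 all but vowel. The RSA also compares an equal-weight with a tone-weighted model. The gap is in P1 and in how P1 and P2 are read.

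**A reader might infer a false-positive rate for P1.** Under a tone-only deficit δ, a pooled multi- minus single-feature amplitude contrast with P1's list has expectation (3/3 − 1/3)δ = 0.67δ. With δ = 0.5 SD, 30 per group and ρ = 0.3, 0.5 or 0.7, it would be significant in 46%, 59% or 81% of studies. These figures only illustrate a contrast that the article does not specify. P1 concerns variance explained, P2 names no such contrast, and δ and ρ are assumed, so they are not error rates of either prediction.

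**Conclusion.** The point holds for P1. Its list is inconsistent with sections 1.2.2 and 1.4 and Table 1, and the omitted condition is the only combination that can distinguish a tone deficit from an integration deficit. This rests on the article's own condition lists and on no assumed effect size. For P2 the finding is narrower: the list is sound, but a reduction confined to it does not by itself support integration over tone.

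The consequence is one of interpretation in a study declared exploratory. The C + V data are part of the design, so nothing is lost that cannot be recovered by rewording and one named contrast. No false-positive percentage can be attached to P1 or P2 from what the article states.

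**What to change.** 1. Add C + V to P1's list so that it matches sections 1.2.2 and 1.4 and Table 1.
2. Keep P2 as a tone prediction with its present list.
3. State that P1 and P2 support an integration account, rather than the tone-specific one in Question 4, only if C + V is also affected.
4. For MMN amplitudes and factor scores, name one test: the group by consonant-by-vowel interaction on deviant-minus-standard responses, (C+V) minus C minus V. State the expected direction in advance. An equal deficit u in every deviant gives u − u − u = −u, the opposite sign to an integration deficit, so a general reduction could mask one.

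The cost is a change to the text and one set of contrast coefficients. The statistical price is precision: about 2.3 to 2.8 times the standard error of the pooled contrast under the assumptions above, and low power for an extra deficit of 0.5 SD. The result should be reported as an estimate with its confidence interval, and a non-significant interaction should not be read as intact integration.

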#### 3.1.2. RSA-Level Predictions

P4 (Representational Structure): Neural representational dissimilarity matrices (RDMs) in the ASD group will show weaker differentiation between multi-feature deviants (e.g., C + V + T vs. standard) compared to TD children, particularly in the lMMN time window.

P5 (Integration Failure): The fit between neural RDMs and a theoretical “Integrated Features” model (which assumes synergistic processing of C, V, T) will be poorer in the ASD group, especially for V + T and C + V + T conditions.

P6 (Local Bias): The fit between neural RDMs and a “Segmental-Only” model (prioritizing C and V) will be stronger in the ASD group than in TD children, reflecting a local processing bias.

### 3.2. Data-Driven Predictions (Based on MMN Literature)

Predictions are also derived for the t-PCA and RSA analyses from empirical findings across multiple studies (Table 2). They reflect general patterns in the literature and serve as a baseline against which theoretical predictions can be evaluated. They do not assume a local/global dissociation but rather a graded, complexity-dependent deficit.

#### 3.2.1. t-PCA-Level Predictions

P7 (Amplitude Attenuation): Across all conditions (with the exception of vowel deviation), the ASD group will show lower factor scores for MMN components, with the most severe reductions in multi-feature conditions.

P8 (Latency Prolongation): Peak latencies of eMMN and lMMN components will be systematically delayed in the ASD group, with delays increasing as feature complexity rises.

P9 (Component Blurring): The temporal separation between eMMN and lMMN components will be less distinct in the ASD group, suggesting a breakdown in the normal cascade of auditory processing stages.

#### 3.2.2. RSA-Level Predictions

P10 (Weaker Representations): Neural RDMs in the ASD group will show lower overall dissimilarity between deviants and standards across all conditions, with the greatest reduction in C + V + T.

P11 (Atypical Weighting): The fit between neural RDMs and a “Complexity-Weighted” model (which predicts linear degradation with added features) will be stronger in the ASD group than in TD children.

P12 (Hemispheric Asymmetry): Representational dissimilarity in the left hemisphere will be disproportionately reduced in the ASD group, particularly for tone-involving and multi-feature conditions, reflecting a lack of typical left-hemisphere specialization for speech.

The dual-prediction framework allows us to test competing accounts of speech processing in ASD. The predictions are focused on measurable outcomes (overall MMN amplitude, latency, and representational structure) rather than on speculative subcomponents. While we will use t-PCA to decompose the ERP signal and ensure accurate extraction of the MMN, we do not make strong a priori predictions about the distinct roles of early vs. late MMN due to the lack of specific empirical evidence in the ASD literature for multi-feature speech paradigms. Instead, any differences in the temporal dynamics of the MMN will be explored post hoc and reported as exploratory findings, not as confirmatory predictions. By grounding our predictions in established frameworks and focusing on robust, falsifiable outcomes, we ensure a transparent and rigorous evaluation of how Mandarin-speaking children with ASD process and integrate speech features.

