##### Step 2: Calculating Neural RDM

Neural RDMs were computed based on ERP data, focusing on specific time windows (e.g., eMMN, lMMN, P3a). For each stimulus, the mean amplitude in the relevant time window was extracted. The neural dissimilarity between each pair of stimuli was quantified using either Euclidean distance or Pearson correlation. This process was repeated for each time window of interest, resulting in a series of neural RDMs.

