##### Step 3: Comparing Neural RDM with Theoretical Models

To assess how well neural responses align with theoretical models, we compute Spearman’s rank correlation between each neural RDM and the candidate theoretical RDMs. This comparison is performed separately for each time window (eMMN, lMMN, P3a). For group-level comparisons, we conduct the RSA separately for individuals with ASD and TD groups to examine potential differences in how speech features are neurally represented. We use permutation testing combined with cluster-based correction to control multiple comparisons and assess significant differences between groups.

These models assume that phonological features contribute additively to auditory dissimilarity, consistent with the view that early auditory encoding tracks separable acoustic dimensions (e.g., pitch, formant structure, place of articulation) without strong nonlinear interactions. The use of weighted models reflects the hypothesis that tone, vowel, or consonant cues may be differentially salient in perception—especially in tonal languages like Mandarin. While interactive or nonlinear RDMs could in principle be constructed (e.g., hierarchical cue interactions or phonological feature geometry), they require stronger theoretical constraints and larger datasets to validate. Thus, the current additive scheme balances theoretical interpretability, perceptual relevance, and statistical robustness. We employed RSA because it extends beyond univariate amplitude analyses by leveraging multivariate patterns of neural responses, allowing detection of distributed representational differences even when traditional ERP measures yield weak or non-significant effects. This approach is highly suitable for multi-feature paradigms, as it can capture subtle shifts in neural encoding across complex feature combinations and evaluate their alignment with theoretically derived perceptual models [80].

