We employ two analytical approaches, temporal PCA and RSA. t-PCA decomposes the ERP waveform into latent components (e.g., early and late MMN), isolating overlapping neural responses and increasing sensitivity to group differences, particularly valuable in pediatric data where peak latency and morphology can vary. By extracting factor scores, we can compare the strength and timing of neural responses across conditions and groups. For instance, if two ERP components (such as an early and late MMN) overlap in the 200–300 ms range, t-PCA can help disentangle them into separate factors, allowing us to assess each one’s magnitude in ASD vs. TD children.

In contrast, RSA examines the multivariate structure of neural representations. It quantifies the dissimilarity between brain responses to different stimuli, creating a representational dissimilarity matrix (RDM). We compare empirical RDMs to theoretical models (e.g., “Integrated Features” vs. “Segmental-Only”) to test whether children with ASD represent speech features differently. This approach moves beyond univariate amplitude/latency measures to assess how features are bound into coherent percepts. For example, one model RDM might predict that changing the lexical tone produces large neural dissimilarity (if tone is a salient feature) whereas changing the consonant with the same tone produces a smaller dissimilarity. Another model might predict that any two-feature change (tone + vowel together) yields a bigger neural distance than single-feature changes. We will correlate these model RDMs with the empirical RDMs derived from the EEG data for each group. If TD children’s neural patterns correspond closely to the model emphasizing multi-feature integration, but ASD children’s patterns do not, this would directly support the idea that the ASD group encodes speech features differently. In essence, RSA will tell us how information is represented in the neural activity of each group—whether the brain treats combined feature changes as the sum of their parts or as a unique, salient event, and how this differs between ASD and TD. This multivariate approach is valuable because it moves beyond examining individual ERP peaks and considers the holistic neural response to speech stimuli as a pattern that can be compared to cognitive models.

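### P4, P10 and P12 predict a smaller amount of neural dissimilarity in ASD, but the only RSA statistic named is a rank correlation, which cannot by itself test them and which noise ties to response size

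*Protocol article*

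**What the plan says.** The RSA predictions are of two kinds.

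- **Amount of dissimilarity.** P4 (section 3.1.2) says that RDMs in ASD "will show weaker differentiation between multi-feature deviants (e.g., C + V + T vs. standard) compared to TD children". P10 (section 3.2.2) says that they "will show lower overall dissimilarity between deviants and standards across all conditions, with the greatest reduction in C + V + T". P12 (section 3.2.2) says: "Representational dissimilarity in the left hemisphere will be disproportionately reduced in the ASD group".
- **Model fit.** P5, P6 and P11 concern how well neural RDMs agree with named models.

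The method in section 2.3.4 is of one kind. Step 2 builds the neural RDMs, with distance "quantified using either Euclidean distance or Pearson correlation". Step 3 computes Spearman's "rank correlation between each neural RDM and the candidate theoretical RDMs", by time window and separately by group. It then adds "permutation testing combined with cluster-based correction to control multiple comparisons and assess significant differences between groups", without naming the quantity that is permuted. The Discussion repeats the correlation approach: "We will correlate these model RDMs with the empirical RDMs derived from the EEG data for each group". It says that if TD patterns match the integration model and ASD patterns do not, "this would directly support the idea that the ASD group encodes speech features differently".

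**The concern.** A rank correlation keeps the order of the dissimilarities and drops their size, while size is what P4, P10 and P12 are about. P10 could be entirely true and the named statistic could show nothing. P12 has a further gap: no hemisphere-specific RDM is described, and the component sites listed in section 2.3.3 (Fz, FCz, Cz) lie on the midline.

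There is also a problem in the opposite direction. In noisy recordings a smaller response against the same noise gives a less reliable RDM, and a less reliable RDM correlates less with any model. P7 predicts lower MMN factor scores in ASD. If that alone were true and feature coding were identical in the two groups, the ASD fit would still tend to be poorer. The study sets out to separate competing accounts, so a fit difference driven by amplitude could support the wrong one.

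**Working it through.** **Inputs from the article.** Eight syllables coded on tone, vowel and consonant (Table 3); unit or doubled feature weights (Step 1); 980 standards and 980 deviants over seven types, so 980 / 7 = 140 per deviant (section 2.2.2); 30 children per group (section 2.1.2). **Assumed, because the article gives no amplitude or SD:** noise SD of 0.25 to 4 relative to a unit feature effect, 3 or 30 channels, and one RDM per child.

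**1. Reproduce the model RDMs.** Counting changed features over 8 × 7 / 2 = 28 pairs gives 12 pairs at 1, 12 at 2 and 4 at 3. The base range is 1 to 3 and the weighted maximum is 4, as Step 1 states. Mean base dissimilarity is (12 + 24 + 12) / 28 = 1.71.

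**2. Uniform loss, no noise.** If every distance d becomes c·d with c > 0, the ranks are unchanged and so is rho. Numerically (30 channels), scaling the response to 0.5 and 0.25 took mean Euclidean distance from 5.87 to 2.94 and 1.47. Rho with the base model was 0.883 each time, and the other three models were equally unaffected.

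**3. Graded loss of the kind P10 describes, no noise.** Let distances follow the feature count and cut single, dual and triple changes by 10, 20 and 30%. The values 1, 2, 3 become 0.9, 1.6, 2.1. The mean falls to (12 × 0.9 + 12 × 1.6 + 4 × 2.1) / 28 = 1.37. The order is intact, so rho stays at 1.00.

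**4. Pearson option.** The distance 1 − r(x, y) equals 1 − r(cx, cy) for c > 0. Amplitude scale is then gone in Step 2, before any comparison.

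**5. With noise and identical coding.** Per-child fits to the base model were compared by two-sided t-test at 0.05, 30 per group, 100 runs per cell. Percentage of runs with a significantly poorer fit in the reduced group:

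| Noise SD | 3 ch., 0.7 | 3 ch., 0.5 | 30 ch., 0.7 | 30 ch., 0.5 |
|---|---|---|---|---|
| 0.25 | 49 | 74 | 69 | 98 |
| 0.5 | 71 | 92 | 98 | 100 |
| 1 | 55 | 86 | 100 | 100 |
| 2 | 22 | 38 | 97 | 100 |
| 4 | 5 | 5 | 21 | 42 |

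With no loss the rate was 0 to 5%. As an example of the shift, at 30 channels and SD 1 a halved response took mean fit from 0.61 to 0.24.

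At a milder response of 0.8, one set of settings gave 12 to 62%. Others gave 8 to 29% with 3 channels and 64 to 98% with 30. Letting response size vary between children lowers the top of that range.

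**6. Which models are affected.** A synergistic model that rises with the number of changed features has the same rank order as the base model, so Spearman treats the two alike. Fit to a tone-free segmental model also fell.

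**7. A direct level outcome.** The mean of the seven standard-deviant distances reads a halved response correctly without noise: 3.40 / 6.79 = 0.50. With noise SD 1, plain Euclidean distance gives 6.79 / 9.12 = 0.74, because noise inflates both groups' distances. The level outcome therefore needs a cross-validated distance.

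**The case against.** Step 3 introduces Spearman only to judge alignment with models, which is what P5, P6 and P11 need. The neural RDM from Step 2 is itself available for P4, P10 and P12, and the permutation sentence speaks of group differences without excluding a test on RDM cells. The article is condensed and the study exploratory. All of that stands. A reader might infer that the three predictions have no test anywhere; the text supports only that none is named and that the named statistic cannot serve alone.

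A reader might also infer that a plain level loss would go unseen, or would be credited to failed integration throughout. The documents do not support this. The t-PCA arm compares amplitudes in µV directly (section 2.3.3), P7 predicts the loss, and the Discussion assigns a general amplitude reduction to the data-driven account. The artefact lowers segmental-model fit too, whereas P6 and P11 predict stronger fit in ASD, so it does not imitate the full predicted pattern.

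Nor is rho always blind to a graded loss. If single, dual and triple distances kept 0.9, 0.5 and 0.3 of their level, 1, 2, 3 would become 0.9, 1.0, 0.9. The order breaks and noise-free rho falls to 0.47.

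What remains is more than an omitted detail. The article states outcomes and names a statistic that does not measure them, and it fixes a reading of poorer fit that response size alone can produce.

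**Conclusion.** The point holds in two limited parts.

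- **Exact, free of assumptions:** Spearman fit does not change under uniform or order-preserving loss, so it cannot by itself test P4, P10 or P12. No level quantity and no hemisphere-specific RDM is named.
- **Direction clear, size uncertain:** with noise, an amplitude loss in ASD lowers fit to the models even when coding is identical. Roughly 10 to 60% false poorer fit at a response of 0.8 is an order of magnitude. It depends on noise level, channel count, per-child RDMs and a uniform loss, none of which the article fixes. Larger losses give higher rates, except where noise is so high that fit is near zero in both groups.

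The plan should be changed. Neither the t-PCA analysis nor the design is in question.

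**What to change.** In Step 3, separate the two kinds of RSA outcome.

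- **P4, P10, P12.** Compare groups by label permutation on the deviant-standard distances: the mean over the seven cells and each cell, and left versus right lateral sites for P12. Use a split-half cross-validated Euclidean distance, and not the Pearson option for these outcomes.
- **P5, P6, P11.** Keep Spearman fit. Interpret a group difference only relative to each group's split-half RDM reliability (noise ceiling) and alongside the t-PCA amplitude result. Qualify the Discussion sentence on different encoding accordingly.

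The cost is analysis wording and a little code on the same recordings. Split halves leave at most 140 / 2 = 70 trials per deviant per half before artefact rejection, so single-child distances will be noisier. A few more RSA tests enter the corrected family.
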